**Methods:**

Patients with squamous cell carcinoma of the head and neck (*n* = 144), treated with radiotherapy, will be randomly assigned to one of 3 comparison groups: pre-radiotherapy supervised exercise, post-radiotherapy supervised exercise and autonomous exercise, stratifying by human papillomavirus infection and previous surgery.

The exercise programme will be carried out in 36 sessions over 12 weeks, combining moderate and high intensity strength and aerobic exercises. The main outcome variable is the change in lean body mass at 6 months measured by bioimpedance, while secondary variables are functional capacity, symptoms, quality of life and adverse effects. Longitudinal generalised mixed models will be used for the analyses of the repeated measurements at 3, 6, and 12 months after baseline.

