## Methods/design

### Trial design

The SEHNeCa project is a multicentre, randomised, controlled clinical trial with three arms. Patients are recruited by the radiation oncologist at the patient’s first visit to the radiation oncology department, where they are asked to participate in the programme. Four assessments are made of all the participants, regardless of the group they belong to, at 0, 3, 6 and 12 months.

The baseline assessment will be performed during the same week as recruitment. After randomisation, the pre-radiotherapy group will start the supervised PE programme (at least 7–10 days before starting radiotherapy). The control and post-radiotherapy groups will initially receive physical activity guidelines that they can perform independently. The post-radiotherapy group will start supervised training 4–6 weeks after finishing radiotherapy and the control group will not have supervised training.

All the patients will receive follow-up by the endocrinology service (before radiotherapy, during radiotherapy, at the end of radiotherapy and one month, 3 months, 6 months and 12 months after the end of radiotherapy) in which they will receive screening and assessment of nutritional status as well as individualised nutritional intervention following international guidelines [19], which may include nutritional advice, oral nutritional supplementation, and/or insertion of a feeding tube as required by each patient (Table 1) (Fig. 1).

**Table 1 Tab1:** SEHNeCa Programme timeline

Follow up	D0	W1	W2		W3		W4		M2		M3		M4	M5	M6	M7	M12	M18
**Diagnosis and recruitment**	**X**																	
**Nutritional evaluation**		**X**									**X**				**X**		**X**	**X**
**Radiation oncology evaluation**	**X**										**X**		**X**		**X**		**X**	**X**
**Radiotherapy**					X													
**Measurements**		**X**											**X**			**X**	**X**	
**Supervised Exercise Intervention**			**PRE-RADIOTHERAPY GROUP**															

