### Effectiveness: primary study outcomes

Change in Lean Body Mass (kg), measured by using an Inbody 770 bioimpedance analyser (In-body, Seoul, Korea).

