### Statistical analysis

Differences between treatment groups in changes in outcome variables will be estimated on an intention-to-treat basis. We will use linear mixed models for longitudinal analysis of repeated measurements of continuous outcomes (SAS PROC MIXED) and generalised logistic mixed models for dichotomous outcomes (SAS PROC GLIMMIX), considering intercept and time courses as random effects and testing the significance of the interaction of time slopes for each treatment group. No imputation method will be used to handle missing data, as longitudinal mixed-effect models based on maximum likelihood estimation are more appropriate for handling missing data than common imputation methods such as the last observation carried forward, complete case analysis, or other possible forms of imputation [29].

A sample size of 40 patients per group (120 in total) will give 80% power to the study to detect as significant (0.05) the difference at six months in a mean lean body mass loss of 25% between the control and rehabilitation groups, and of 12% between the rehabilitation and prehabilitation groups, corresponding to an estimated mean lean body mass loss from baseline of 4.8 kg (9.1%) in the control group, 3.6 kg (6.8%) in the rehabilitation group, and 3.2 kg (6%) in the prehabilitation group (standard deviation 2,4 kg). With an anticipated drop-out rate of 20%, we plan to enrol 144 patients (48 per group).

During these first 12 months of recruitment, the radiation oncology departments of Basurto and Cruces University Hospitals have attended 161 eligible patients, 112 met the inclusion criteria, of whom 63.4% agreed to participate in the study. Therefore, we expect that the recruitment period will last 24 months.

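### The only test the plan names compares 12-month time slopes between groups, while the primary outcome and the sample size concern the 6-month change in lean body mass

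*Protocol article*

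**What the plan says.** The abstract of the protocol article names the endpoint and its time point: "The main outcome variable is the change in lean body mass at 6 months measured by bioimpedance". The section on primary study outcomes repeats the variable without a time point: "Change in Lean Body Mass (kg), measured by using an Inbody 770 bioimpedance analyser". The Statistical analysis section builds the sample size on the six-month difference: mean losses of 4.8 kg (control), 3.6 kg (rehabilitation) and 3.2 kg (prehabilitation), SD 2.4 kg, 40 per group, 80% power.

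On the analysis, the same section opens with "Differences between treatment groups in changes in outcome variables will be estimated on an intention-to-treat basis" and gives no time point. It then describes mixed models with a random intercept and a random time course, and "testing the significance of the interaction of time slopes for each treatment group". No other test is named. The Trial design section places the assessments "at 0, 3, 6 and 12 months", and the abstract brings the 3-, 6- and 12-month measurements into the model.

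On delivery, Trial design states: "The control and post-radiotherapy groups will initially receive physical activity guidelines that they can perform independently". The pre-radiotherapy arm starts its 12-week supervised programme after randomisation. The post-radiotherapy arm starts its programme 4-6 weeks after radiotherapy ends. The control arm has no supervised training.

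**The concern.** A group-by-slope interaction asks whether the arms differ in average rate of change over the whole year. The primary outcome asks whether they differ in change at month 6. The two questions coincide only if the difference between arms grows in a straight line from baseline to month 12.

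The design gives little reason to expect that. Control and post-radiotherapy patients receive the same exercise advice until supervised training begins in the latter arm, so those two arms should separate only from then on. The pre-radiotherapy arm has its supervised training at the start, so its advantage may appear early and then level off.

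If the slope test decides the trial, a real 6-month benefit can be missed, and a difference present only at month 12 can be read as success on a 6-month endpoint. If the slope test and a 6-month comparison are both run and disagree, nothing in the article says which one counts.

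**Working it through.** **Inputs from the protocol article.** Times 0, 3, 6 and 12 months; 40 per group; SD of 6-month change 2.4 kg; planned differences 4.8 - 3.6 = 1.2 kg (rehabilitation vs control) and 4.8 - 3.2 = 1.6 kg (prehabilitation vs control). Alpha is 0.05, taken as two-sided because the article does not say.

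**The plan's own figure.** For a direct 6-month contrast, SE = 2.4 × √(2/40) = 0.537 kg. For 1.2 kg, z = 1.2/0.537 = 2.24 and power = Φ(2.24 - 1.96) ≈ 61%, not the stated 80%. That shortfall is a separate matter; 61% serves here only as the benchmark for the slope test.

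**Slope weights.** With complete data and a random intercept and slope, the generalised least-squares slope equals the ordinary one, with weights (t - 5.25)/78.75. Here 5.25 is the mean time and 78.75 the sum of squared deviations.

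| Month | Weight | Share of absolute weight |
|---|---|---|
| 0 | -0.0667 | 35% |
| 3 | -0.0286 | 15% |
| 6 | +0.0095 | 5% |
| 12 | +0.0857 | 45% |

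Table 1 appears to mark measurements at week 1 and months 4, 7 and 12. At those times the third visit has about 8% and month 12 about 42%. The conclusion is the same.

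**Implied 6-month difference** = 6 × Σ(weight × group difference). For rehabilitation vs control I take no difference at month 3 and 1.2 kg at month 6:
- persists at 1.2 kg to month 12: 6 × (0.0095 × 1.2 + 0.0857 × 1.2) = 0.69 kg
- halves to 0.6 kg: 6 × (0.0095 × 1.2 + 0.0857 × 0.6) = 0.38 kg
- gone by month 12: 6 × 0.0095 × 1.2 = 0.07 kg
- grows to 2.4 kg: 6 × (0.0095 × 1.2 + 0.0857 × 2.4) = 1.30 kg

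For prehabilitation vs control, month 3 enters with a negative weight, so an early gain counts against the arm. A constant 1.6 kg advantage at months 3, 6 and 12 gives 6 × 1.6 × (-0.0286 + 0.0095 + 0.0857) = 0.64 kg.

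**Power of the slope test.** The article does not split the 2.4 kg SD into random-slope and residual parts, so this is an assumption. I set 36·s² + 2·e² = 2.4² = 5.76 (s the slope SD, e the residual SD) and let the slope part be 0% to 75% of that variance. The SD of a patient's slope is √(s² + e²/78.75), and the SE of a group difference is that SD × √(2/40).
- 0%: s = 0, e² = 2.88; slope SD 0.191, SE 0.0428 kg/month
- 75%: s² = 0.12, e² = 0.72; slope SD 0.359, SE 0.0804 kg/month

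| Group difference at 0/3/6/12 months (kg) | Slope power, 0% to 75% | Direct 6-month contrast |
|---|---|---|
| 0/0/1.2/1.2 | 76% to 30% | 61% |
| 0/0/1.2/0.6 | 31% to 12% | 61% |
| 0/0/1.2/0 | 6% to 5% | 61% |
| 0/0/1.2/2.4 | 99.9% to 77% | 61% |
| 0/0/0/1.2 (nothing at month 6) | 67% to 25% | 5% (alpha) |

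**The case against.** Linear time is nowhere stated outright. In the Statistical analysis section the word linear qualifies the mixed model, not time, and the opening sentence about differences in changes is compatible with deriving a 6-month change from the fit. Coding of time and contrast statements are often left to an analysis plan, which may exist. This stands as a caution, and the figures above are conditional on the linear reading. That reading is nevertheless the natural one for random time courses and time slopes, and under it any 6-month change derived from the model is just six times the slope. The point is also not that detail is missing: the article names a test, and that test does not address its own endpoint.

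A reader might go further and infer three things that the document does not support.

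- *That the design rules out straight lines.* The staggered start argues strongly against linearity for rehabilitation vs control. For prehabilitation vs control, training begins soon after baseline, so a straight line is doubtful but not excluded. The month at which rehabilitation starts is itself inferred, since the article gives no radiotherapy duration.
- *That the slope test always loses power.* It does not. If the difference keeps growing to month 12 it beats the 6-month contrast. With a persisting difference and little slope variation it also does (76% vs 61%), because it uses four readings.
- *That a 5% weight makes the slope test invalid.* Month 6 has little weight because it lies near the mean time of 5.25 months. If the difference were truly linear, six times the slope would still estimate the 6-month difference without bias.

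**Conclusion.** The point holds. The primary outcome and the sample size concern the 6-month change; the only named test concerns the slope over 12 months. On the linear-time reading with complete data, the weights (5% at month 6, 45% at month 12) and the implied differences of 0.69, 0.38 and 0.07 kg need no variance assumption, only the assumed trajectories. The power ranges also rest on the assumed 0-75% slope share, so no single power figure should be quoted.

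The direction of the power change depends on a trajectory the article does not give. What does not depend on it is that the named test can disagree with the endpoint in both directions: it can have almost no power for a 1.2 kg difference at month 6 that has gone by month 12, and it can reject in 25-67% of trials when only month 12 differs. Because this determines the primary conclusion, it should be settled before analysis.

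**What to change.** State that the primary test is the between-group contrast in 6-month change in lean body mass, taken from a mixed model with time as a categorical factor (0, 3, 6 and 12 months) and a group-by-time interaction, preferably adjusted for baseline lean mass. The covariance structure can be left to the trial statistician. Keep the slope interaction as a secondary analysis, and add the 6-month time point to the primary-outcome section so that it matches the abstract.

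The cost is one paragraph and different statements in the same SAS procedure, with no new data. The downsides are a few more parameters to estimate and less power than the slope test if group differences do grow linearly to month 12.

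### The 80% power claimed for two pairwise comparisons is wrong on the plan's own figures: about 60% for control vs rehabilitation and 11% for rehabilitation vs prehabilitation

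*Protocol article*

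**What the plan says.** The sample size paragraph under Statistical analysis says that 40 patients in each arm "will give 80% power to the study to detect as significant (0.05) the difference at six months". Two pairwise contrasts are named as the differences meant. The first sets control against rehabilitation and is put at 25%. The second is added with the words "and of 12% between the rehabilitation and prehabilitation groups".

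The same paragraph then gives the assumed losses behind these percentages. For control the figure is 4.8 kg (9.1%), and for rehabilitation it is 3.6 kg (6.8%). The third arm and the spread are given as "3.2 kg (6%) in the prehabilitation group (standard deviation 2,4 kg".

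The significance level appears only as 0.05. The paragraph states no sidedness, multiplicity adjustment or within-patient correlation, and it does not mention an overall three-group test as the basis of the power.

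The Abstract and the last paragraph of the Introduction make the best time for supervised exercise, before or after radiotherapy, an objective of the trial.

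**The concern.** The paragraph gives one power figure, at one sample size, one SD and one significance level, to two differences of which one is three times the other. Required sample size varies with the inverse square of the difference, so it differs by 3² = 9. Both claims cannot be true together, whatever test is used.

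What is at stake is mainly the timing question, because rehabilitation vs prehabilitation is the smaller of the two differences. If the trial has little chance of detecting it, a non-significant result is the expected one. A reader who has been told that this contrast had 80% power would take such a result as evidence that timing makes no difference. If the first contrast also falls short, the comparison of post-radiotherapy supervised exercise with control has a sizeable chance of missing the benefit the plan assumes.

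**Working it through.** **Inputs** (Statistical analysis section): n = 40 per group; SD = 2.4 kg, taken as the between-patient SD of the six-month change; mean losses 4.8, 3.6 and 3.2 kg; alpha 0.05, taken as two-sided and unadjusted. Allocation is 1:1:1 (Randomisation section).

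**Differences**
- Control − rehabilitation: 4.8 − 3.6 = 1.2 kg (1.2/4.8 = 25%, as stated).
- Rehabilitation − prehabilitation: 3.6 − 3.2 = 0.4 kg (0.4/3.6 = 11%; 0.4/3.2 = 12.5%; stated as 12%).
- Control − prehabilitation, not named in the power sentence: 1.6 kg.

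**Where the 80% comes from.** For the overall test of three means, λ = n Σ(μᵢ − μ̄)² / SD². The mean of the three losses is 3.867, and the squared deviations are 0.871 + 0.071 + 0.444 = 1.387. So λ = 40 × 1.387 / 5.76 = 9.63. Power is 78.9% (F test, 2 and 117 df) or 80.0% (2-df chi-square). This is the only calculation tried that returns about 80% at 40 per group.

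**Pairwise power.** The standard error of a difference is 2.4 × √(2/40) = 0.537 kg. The noncentrality is the difference divided by 0.537, with 78 df:

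| Contrast | Difference | Noncentrality | Power (t) | n per group for 80% |
|---|---|---|---|---|
| Control vs rehabilitation | 1.2 kg | 2.24 | 59.8% | 64 |
| Rehabilitation vs prehabilitation | 0.4 kg | 0.75 | 11.4% | 567 |
| Control vs prehabilitation (not named) | 1.6 kg | 2.98 | 83.8% | 37 |

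The normal approximation, n = 2(1.960 + 0.842)² × SD² / difference², gives 63 and 566 per group for the two named contrasts.

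- Both named contrasts significant together: about 3% (simulation).
- Smallest difference detectable with 80% power at 40 per group: about 1.52 kg, larger than either named difference.
- SD needed for 80% at 40 per group: 1.89 kg for 1.2 kg, but 0.63 kg for 0.4 kg. No single SD serves both.
- Half-width of the 95% confidence interval for any pair: 1.98 × 0.537 = 1.06 kg, which is 1.06/0.4 ≈ 2.7 times the assumed timing effect.

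**Other readings** (t-test power for 1.2 kg and 0.4 kg)

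| Reading | 1.2 kg | 0.4 kg |
|---|---|---|
| One-sided 0.05, n = 40 | 71.6% | 18.2% |
| All 48 per group retained, two-sided | 67.9% | 12.8% |
| All 48 per group retained, one-sided | 78.4% | 20.2% |
| 38 per group (48 less 20% is 38.4) | 57.6% | 11.1% |
| Bonferroni for three pairs, n = 40 | 42.1% | 4.9% |

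None brings both contrasts to 80%, and none lifts the 0.4 kg contrast much above 20%.

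**The case against.** The strongest defence is that the 80% is a sound calculation described loosely. It agrees with the overall test of the three stated means, and the planned test of group-by-time slopes is naturally a joint test across three groups. On that view the two percentages only describe the assumed pattern of means. This probably explains how the figure arose. It does not make the sentence true, because the sentence attaches the power to two named pairs and mentions no overall test. Nor does a significant overall test show which groups differ. With these means it is driven mainly by prehabilitation vs control.

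A second defence is that 59.8% assumes an unadjusted two-sample test, whereas the plan uses a longitudinal mixed model that may be more precise. The document gives no correlation, so the gain can only be assumed. If the SD shrinks by √(1 − r²) with r between 0.5 and 0.7, power for 1.2 kg rises to about 72–87%, while power for 0.4 kg is still only 14–18%. To reach 80%, the 1.2 kg contrast would need r of about 0.62 and the 0.4 kg contrast about 0.96, which is not credible. So the shortfall on the first contrast depends on the unadjusted test, whereas the shortfall on the timing contrast does not.

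It is also fair to say that the protocol nowhere states that a non-significant timing result would be read as equivalence. That risk lies with readers who rely on the stated power.

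**Conclusion.** The concern holds. On the plan's own inputs, 40 per group gives about 60% power for control vs rehabilitation and 11% for rehabilitation vs prehabilitation, not 80% for each. The 80% fits only the overall three-group test, so it appears to be a valid figure attributed to the wrong hypotheses.

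The exact percentages assume two-sided 0.05 without multiplicity adjustment, and that 2.4 kg is the SD of the six-month change. The 60% also assumes no precision gain from repeated measurements. The main conclusion needs none of these: no single sample size or SD gives 80% for both contrasts, and the timing contrast is far from powered under any plausible reading. Because timing is a stated objective, the sentence must be corrected.

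**What to change.** Replace the power sentence with text along these lines:

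> Forty evaluable patients per group give about 79% power for the overall three-group test at six months (mean losses 4.8, 3.6 and 3.2 kg; SD 2.4 kg; alpha 0.05). Pairwise two-sided power is about 84% for prehabilitation vs control, 60% for rehabilitation vs control and 11% for prehabilitation vs rehabilitation. The last contrast is not powered; it will be estimated with a 95% confidence interval (expected half-width about 1.06 kg), and non-significance will not be read as equal effects of timing.

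The authors should confirm that the overall test was the basis of their calculation. If they relied on a precision gain from the mixed model, they should state the assumed correlation. The figures above apply to the 40 evaluable patients the plan states. If the text is instead based on 38 per group after drop-out, they become 76.6% overall and 82%, 58% and 11% pairwise.

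The cost is protocol wording and a less favourable stated power. No extra patients are needed. As 71 patients are already included (Strengths of the study), the correction should be made before results are known.

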### Randomisation

Randomisation is carried out on a central basis through the coordinating committee. This will be made up of the organization responsible for the study’s management and the researchers. The committee will be blind to the assignment of patients in the comparison groups and will convene in the Primary Health Research Unit of Bizkaia.

The 120 patients included in the study will be randomly assigned and consequently registered and attached to one of the three study groups in a 1:1:1 ratio, through randomisation by random blocks of 3 or 6 patients. Patients are stratified according to HPV status and previous surgery yes/no.

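### The sample-size figures conflict: 144 enrolled with 20% drop-out leaves about 115 of the 120 required, and the Randomisation section randomises only 120, which would leave 96.

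*Protocol article*

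**What the plan says.** The Statistical analysis section sets the requirement: "A sample size of 40 patients per group (120 in total) will give 80% power to the study". It assumes mean lean body mass losses at six months of "4.8 kg (9.1%) in the control group, 3.6 kg (6.8%) in the rehabilitation group, and 3.2 kg (6%) in the prehabilitation group", with "standard deviation 2,4 kg". It then allows for attrition: "With an anticipated drop-out rate of 20%, we plan to enrol 144 patients (48 per group".

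Two other places give the number allocated. The Methods paragraph of the abstract describes "Patients with squamous cell carcinoma of the head and neck (*n* = 144), treated with radiotherapy", and says that these are the patients assigned at random to the three groups. The Randomisation section says "The 120 patients included in the study will be randomly assigned", in a 1:1:1 ratio with blocks of 3 or 6.

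**The concern.** There are two separate problems with the same set of figures.

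First, the drop-out allowance was added to the requirement instead of being taken from the number enrolled. At the anticipated drop-out rate, the planned enrolment does not leave the 40 per group to which the same paragraph attaches 80% power.

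Second, the article gives two different numbers for the same act of random assignment: 144 in the abstract and 120 in the Randomisation section. The 120 is also the number required for power, so it appears once as the count before losses and once as the count after them.

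The second problem matters more. The Randomisation section is where someone preparing an allocation list would look. If the list or recruitment stopped at 120, the trial would end well below its stated size. As written, stopping at 120 or at 144 could each be called the planned size.

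**Working it through.** **Inputs, all from the Statistical analysis section unless noted.** Required: 40 per group, 120 in total. Drop-out: 20%. Planned enrolment: 144, 48 per group. Mean losses: 4.8 kg (control), 3.6 kg (rehabilitation) and 3.2 kg (prehabilitation). SD: 2.4 kg. Significance level: 0.05; sidedness is not stated and two-sided is assumed here. Number randomised: 120 (Randomisation section) or 144 (abstract).

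**Step 1. Reproduce the plan's figure.** 120 × (1 + 0.20) = 144 and 40 × 1.20 = 48. Both stated figures are matched exactly, so this is how they were obtained.

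**Step 2. Apply the drop-out to those enrolled.**
- Remaining from 144: 144 × 0.80 = 115.2, or 38.4 per group.
- Drop-out that 144 can absorb while leaving 120: 1 − 120/144 = 16.7%.
- Enrolment needed to leave 120: 120/(1 − 0.20) = 150, or 50 per group.

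**Step 3. Apply the drop-out to the figure in the Randomisation section.** 120 × 0.80 = 96, or 32 per group.

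**Step 4. Could 144 be the number enrolled and 120 the number randomised?** The abstract says that the 144 are randomly assigned. The sample-size paragraph splits the 144 into 48 per group, and groups exist only after allocation. No section describes losing 24 patients before randomisation. Such a loss would be 24/144 = 16.7%, not the stated 20%. The text does not support this reading.

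**Step 5. Effect on power.** The article does not name the test behind its 80%. The calculation used:
- a three-group F-test with noncentrality N × f², where f² = variance of the three means / SD² = 0.4622/5.76 = 0.0802;
- two-sided two-sample t-tests with noncentrality d / (2.4 × √(2/n)), where d is the difference in means and n the number per group.

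| Comparison | 40 per group | 38.4 per group | 32 per group |
|---|---|---|---|
| Three-group F-test | 78.9% | 77.1% | 68.5% |
| Prehabilitation vs control (1.6 kg) | 83.8% | 82.2% | 74.7% |
| Rehabilitation vs control (1.2 kg) | 59.8% | 58.0% | 50.4% |

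The F-test comes closest to the stated 80%. If the tests were one-sided, the power at 40 and 32 per group would be 90.5% and 84.0% for the 1.6 kg difference, and 71.6% and 63.1% for the 1.2 kg difference. The levels rise, but the loss from 40 to 32 per group remains.

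**The case against.** The arithmetic is not in dispute; the weight given to it can be.

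- **The inflation slip is small.** It amounts to 4.8 patients, under 2 per group, and about 2 points of power. Given an assumed SD and an anticipated drop-out rate, that would not change the trial. This stands.
- **The 120 is probably a leftover from before inflation.** The abstract and the sample-size paragraph both say 144, and the recruitment forecast agrees: 63.4% of 112 is 71 patients in 12 months, so 24 months gives about 142. The 96-patient outcome is therefore a worst case, not the expected result. This also stands, but the section on allocation still carries the wrong number.
- **The analysis uses partial data.** The planned likelihood-based mixed models keep patients who leave after an early assessment. The 115 and 96 are thus patients who complete, and the powers above are complete-case powers that somewhat overstate the loss. This softens the size but does not reconcile the figures, since the sample size was set for the six-month difference.
- **Restoring 40 per group would not give 80% power for the two contrasts the paragraph names.** Even with no drop-out, power is about 60% for rehabilitation vs control and about 11% for rehabilitation vs prehabilitation. That is correct, but it is a separate matter. It does mean that any restated power must name its test.

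**Conclusion.** The concern holds on both counts. The planned 144 does not leave 120 after 20% drop-out: it leaves about 115, and it covers 16.7% loss. The Randomisation section's 120 contradicts the 144 in the abstract and in the sample-size paragraph.

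The first error is minor, at about 2 points of power. The second is more serious, but only if the figure of 120 is followed: about 96 patients would then remain, and overall power would fall by about 10 points against 40 per group. These sizes rest on the protocol's means and SD, a two-sided 0.05 level and a complete-case analysis at six months. The inconsistency of the counts rests on none of these.

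The Strengths section reports 71 patients included so far, short of every candidate total, so the target can still be settled before it decides when enrolment stops.

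**What to change.** 1. In the Randomisation section, change the number randomised from 120 to 144, and check that the allocation list runs to 144.
2. In the sample-size paragraph, state either that 144 with 20% drop-out leaves about 115 patients (38 per group), with the power at that size and the test it refers to, or that 144 covers 16.7% drop-out.

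This is a change of wording in two places and needs no extra patients.

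If the sponsor wants to keep 40 per group at 20% loss, the figure is 150 (50 per group) in every place. That adds 6 patients, about one month at 71 per year (71/12 = 5.9 per month). It is also a formal change of sample size in a trial that is already recruiting, so it costs more than a correction of wording. It is optional, because the conflict is resolved without it.
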